### Planned Analyses

Prior to analysis, univariate, bivariate, distributional, and missing data characteristics of the data will be examined, and subsequent models will be adjusted (e.g., robust estimators, generalized models, non-parametric approaches) to ensure data-analytic assumptions are met. Baseline data from youths, caregivers, and clinicians will be compared across conditions, and any significant (*p*< .05) differences that emerge will be considered as covariates or moderators in subsequent analyses. Medication use, gender, and race/ethnicity may be examined as covariates and moderators in all outcome models to assess the robustness of effects. Missing data will be accommodated using full information maximum likelihood estimation or multiple imputation. Due to the low risk nature of this intervention, there will be no interim analyses; all data analyses will be conducted when data collection is complete.

### Aim 1

The effectiveness of FIRST compared to UC will be assessed using longitudinal multilevel models estimated with repeated measures at level 1 (5 +observations; random effects) nested within participants at level 2 *(N=* 180, random effects) nested within clinicians at level 3 *(N=* 24; random effects). Clinics will be modeled via dummy-coded fixed effects at level 3 and time will be modeled as linear or log-linear days since baseline. The effectiveness of FIRST vs. UC will be tested via the contrast term for the slopes of change in each condition. A significant (*p*< .05) contrast indicates that one group improved more rapidly than the other. The magnitude of this effect will be examined through the standardized mean difference effect size of the slope contrast (i.e., difference between the two conditions’ slopes divided by the square root of the overall slope variance), with clinical significance examined in terms of model-implied outcomes at 6, 12, and 18 months within each group. To complement these primary symptom trajectory outcomes, we will also examine change in total number of diagnoses on the modified MINI-KID-P at post-treatment using generalized linear models, controlling for baseline diagnoses.

### Aim 2

Latent growth curve (LGC) mediation models will be estimated to test measures of regulation of negative emotions as a candidate mechanism of change. Mediation will be specified using the randomly assigned intervention condition (FIRST vs. UC) as an observed variable, and latent intercepts (baseline levels) and slopes (linear change) in primary and secondary outcomes based on multiple occasions of measurement (e.g., weekly, 0–3-6–9-12–18 months). The LGC models will allow for assessment of whether changes in negative affect (e.g., reduction in negative emotions, increases in coping) that occur early on (e.g., weekly during treatment, or 0–3-6 months) account for symptom change that occur in the long-term (e.g., CBCL/YSR outcome trajectories through 18 months). In this way, these models will achieve the requisite temporal sequence to establish that a variable actually functions as a mechanism of change for mediation.

### Aim 3

Aim 3 analyses will be conducted in an exploratory manner. Data collected from clinicians at baseline in both conditions will be examined in multilevel regression models as level-2 (clinician-level) predictors of level-1 (youth-level) implementation outcomes (e.g., TIEBI-coded adherence and competence). For these models, we will use case-level mean TIEBI scores (i.e., averaging across beginning, middle, and end of treatment scores for each youth) as the outcome variables. As the predictors, we will use scores for measures of clinicians’ baseline knowledge of (KEBSQ), attitudes toward ESTs (EBPAS), motivation to use ESTs (EBTI), and perceptions of organizational climate. Models will be estimated in a hierarchical two-step sequence. In step 1, we will examine these four variables as predictors of implementation outcomes. In step 2, we will test whether these four variables interact with treatment condition; this may clarify whether these evidence-based practice psychological variables predict implementation outcomes differently for those in the FIRST condition as compared to UC.

We used the SPIRIT checklist when writing our report [62].

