All clinicians working at participating clinics (and new clinicians starting at the clinics during the study) are invited to participate and provide written informed consent. Upon enrolling, clinicians are randomly allocated to 1 of 2 conditions: the FIRST condition (i.e., to receive training and other implementation supports in FIRST; see “Intervention Condition: FIRST”) or the UC condition (i.e., to continue providing the treatment they ordinarily provide and believe to be effective; see “Control Condition: Usual Care”). Youth participants who seek treatment via typical referral processes at partner clinics are invited to participate in the study and screened for eligibility by study staff prior to obtaining informed consent from caregivers and assent from participating youths. Youths are then randomly allocated to condition (FIRST vs. UC). To avoid obstructing youths’ access to appropriate care, and to guard against the possibility of important condition differences emerging by chance, a few stratifications and constraints are employed. Random allocation is programed to achieve, approximately, (a) a balance of clinicians’ language fluency (English-only vs. Spanish-bilingual) and education level (doctoral vs. non-doctoral) across conditions; (b) a balance of youth age (younger [7–11] vs. older [12–15]) across conditions; and (c) a ~ 1:1 allocation ratio within each clinical site, for both clinicians and youths.

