#### Additional Services.

Additional services will be assessed via a newly developed measure based on existing measures (e.g., Services Assessment for Children and Adolescents [42, 43]). In this measure, caregivers report whether youths received any non-study related therapy services since the last assessment, and if so, who provided the service and the treatment target. Caregivers also report youth psychotropic medication use, including start dates, end dates, and the types of medications.

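### Covariates are chosen by baseline significance tests between randomised arms, a rule that selects on chance imbalance and will rarely pick the balancing factors the slope model does not name

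*Protocol article*

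**What the plan says.** All points are in the protocol article.

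- **Selection rule (Planned Analyses).** "Baseline data from youths, caregivers, and clinicians will be compared across conditions", and at p < .05 any "differences that emerge will be considered as covariates or moderators in subsequent analyses".
- **Balancing factors (Design).** Allocation is programmed to balance, approximately, clinician language fluency, clinician education level, youth age band ("a balance of youth age (younger [7–11] vs. older [12–15]) across conditions"), and the 1:1 ratio within each clinical site.
- **Aim 1 model (Planned Analyses).** Repeated measures are nested in youths, and youths in clinicians. "Clinics will be modeled via dummy-coded fixed effects at level 3". Age band, language and education are not named. The test is the between-arm contrast of slopes.
- **Medication (Planned Analyses; Additional Services; Table 1).** "Medication use, gender, and race/ethnicity may be examined as covariates and moderators in all outcome models to assess the robustness of effects". The Additional Services measure, taken at baseline and quarterly, records "youth psychotropic medication use, including start dates, end dates, and the types of medications".

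**The concern.** When allocation is random, a significance test on a baseline variable tests a null hypothesis known to be true. A p-value below .05 shows that chance produced an imbalance. It does not show that the variable predicts outcome. Three consequences follow.

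1. The primary model is not fixed in advance. Which variables enter, and whether as covariate or moderator, depends on the data and on what the word *considered* comes to mean.
2. Prognostic variables that happen to be balanced stay out, and the precision they would bring is lost.
3. Variables that allocation forces into balance will seldom reach p < .05. The screen therefore steers away from age band, language and education, the factors the design itself singles out.

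Medication is a smaller, related matter. It is allowed as covariate and moderator without a time limit, yet it is recorded through follow-up. Medication started after allocation may itself respond to the care received, so conditioning on it could remove part of a treatment effect or create an apparent one.

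**Working it through.** **The plan's own figure.** 180 / (1 − 0.15) = 211.8, which rounds up to the stated 212. Nothing below changes the sample size.

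**How often the screen fires by chance.** The article gives no number of tests. The scales it describes suggest many are possible.

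- Youth and caregiver scores: CBCL 3, YSR 3, BFS 3 × 2 informants = 6, TPA 2, PANAS 2 × 2 = 4, Coping Questionnaire 2, MINI-KID-P 1, PTSD-RI-5 2. Total 23.
- Clinician scores: KEBSQ-SF 2, EBPAS 4, EBTI 1, TCU-ORC 4. Total 11.

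That is 34 before demographics. It counts what could be tested, not what the plan says will be. For k independent tests, P(at least one flag) = 1 − 0.95^k and the expected number of flags is 0.05k. The last two columns assume a common pairwise correlation r.

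| k (assumed) | Expected flags | P, independent | P, r = 0.3 | P, r = 0.5 |
|---|---|---|---|---|
| 5 | 0.25 | 23% | 21% | 18% |
| 10 | 0.50 | 40% | 35% | 29% |
| 20 | 1.00 | 64% | 54% | 42% |
| 30 | 1.50 | 79% | 66% | 51% |

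Correlation lowers the chance of any flag but leaves the expected number unchanged.

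**Effect on the test.** This was simulated with 180 youths, one covariate, a single continuous outcome, 40,000 runs and a true difference of 0.42 SD, chosen to give about 0.80 power unadjusted. It is a simplification of the three-level slope model. The covariate–outcome correlations ρ are assumptions.

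*Covariate not balanced by design:*

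| ρ | Type I, p < .05 rule | Power, p < .05 rule | Power, always adjusted |
|---|---|---|---|
| 0.3 | 0.048 | 0.80 | 0.83 |
| 0.5 | 0.043 | 0.81 | 0.90 |
| 0.7 | 0.036 | 0.82 | 0.97 |

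*Covariate exactly balanced by design:*

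| ρ | Type I if left out | Power if left out | Power if included |
|---|---|---|---|
| 0.3 | 0.039 | 0.81 | 0.84 |
| 0.5 | 0.022 | 0.83 | 0.90 |
| 0.7 | 0.006 | 0.88 | 0.98 |

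With adjustment, type I error was about 0.05 throughout. As a check on the second table, exact balance gives a size of 2[1 − Φ(1.96/√(1 − ρ²))] when the factor is left out. At ρ = 0.3 this is 2[1 − Φ(2.055)] = 0.040, in line with the simulated 0.039. Both tables are likely to overstate the effect here. Measurement error and clinician clustering dilute the share of the slope contrast's variance that a factor explains, and the Design section promises only approximate balance.

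**Discretionary use.** A second simplified simulation used 180 youths, 30 independent covariates of which five were prognostic, and no treatment effect. Reporting the more favourable of the unadjusted and flag-adjusted analyses gave a type I error of roughly 6 to 7%.

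**Slope versus intercept.** The tested term is a condition-by-time contrast. A covariate entered only as a main effect shifts the intercept and does not adjust the slope, so a time interaction is needed.

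**The case against.** The strongest reply is that this is a condensed article. A full covariate list belongs in an analysis plan that is not shown, and the Aim 1 text does not claim its list is complete. That stands against any finding resting only on the three unnamed factors. It does not excuse the baseline rule, which is stated outright and which an analysis plan would have to override.

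Four stronger readings are tempting and are not supported.

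- *The model ignores the randomisation factors.* Clinic is one of them and is in the model. The gap concerns the other three.
- *The clinic terms adjust the intercept only.* A level-3 fixed effect can enter the intercept equation, the slope equation or both, and the text does not say which.
- *The primary result will be adjusted for medication started after allocation.* The article says medication "may" be examined, as a robustness check. Later medication is permitted by silence, not stated as intended, so the risk attaches to an optional analysis.
- *The rule inflates false positives.* Applied mechanically, the rule and the omission err on the conservative side. Inflation needs a choice among models after seeing the results, which the wording allows but does not plan.

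The 79% figure should not be quoted alone. It needs 30 independent tests, and many of the baseline scales overlap.

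**Conclusion.** The concern holds for the stated rule. Selecting covariates by p < .05 between randomised arms makes the analysis model depend on chance imbalance, and it will rarely bring in age band, clinician language or clinician education. The probability that it flags something under correct randomisation runs from about 23% (5 independent tests) to 79% (30), and lower with correlated measures. The number of tests is an assumption.

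The expected harm is lost power and a mildly conservative test. Its size depends on how prognostic the factors are, which the article does not say. The possible harm from discretionary use is a modest rise in type I error. The sample size is untouched. The medication point is a needed clarification of an optional analysis, not a fault in the primary contrast.

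**What to change.** 1. Delete the baseline-significance rule. Baseline characteristics can still be tabulated by arm.
2. In the primary slope models, prespecify clinic, youth age band (7–11 vs 12–15), clinician language fluency and clinician education, each with its interaction with time.
3. State that medication, where used as a covariate or moderator, means use before randomisation. Report later medication descriptively by arm.

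**Cost.** This is a wording change. The balancing factors are already known at allocation, medication is already collected with dates, and no analysis is planned until data collection is complete. The price is clinician-level degrees of freedom. With about 24 clinicians, an intercept and condition leave roughly 24 − 2 = 22. Language and education reduce this to 20, and each clinic dummy takes one more; the article does not give the number of clinics. Language may also overlap with clinic if bilingual clinicians are concentrated at some sites, so the plan should say in advance what is dropped or combined if the model cannot be estimated.

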#### Inclusion Criteria.

Youths are eligible to participate if:

They are newly referred for treatment at a partner clinic;They are between 7.0 and 15.9 years of age on the date of caregiver consent;They have at least one scale on the Child Behavior Checklist (CBCL) [30] that is clinically elevated (borderline or clinical range) for symptoms of anxiety, depression, conduct problems, or posttraumatic stress per caregiver report; and,They are fluent in English and their caregiver is fluent in English or Spanish.

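### Aim 2 treats time order as enough to establish a mechanism, but the mediator is not randomised and the main covariate rule is not built to find mediator-outcome confounders

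*Protocol article*

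**What the plan says.** Three statements in the protocol article matter.

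- **Model (Planned Analyses, Aim 2).** Mediation is specified "using the randomly assigned intervention condition (FIRST vs. UC) as an observed variable, and latent intercepts (baseline levels) and slopes (linear change"), for both the primary and the secondary outcomes over repeated measurements. Early change in negative affect or coping is examined to see whether it can "account for symptom change that occur in the long-term (e.g., CBCL/YSR outcome trajectories through 18 months").
- **Conclusion (same paragraph).** The models are said to secure the time order needed to "establish that a variable actually functions as a mechanism of change for mediation". Time order is the only support offered for that conclusion.
- **Covariates (Planned Analyses, opening paragraph).** Baseline data are compared across conditions, and "any significant (*p*< .05) differences that emerge will be considered as covariates or moderators in subsequent analyses". A second sentence adds: "Medication use, gender, and race/ethnicity may be examined as covariates and moderators in all outcome models to assess the robustness of effects". Both sentences precede the three aims, and the first refers to subsequent analyses, so it reaches Aim 2.

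The text does not say whether the slopes are regressed on the latent intercepts.

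**The concern.** Randomisation protects the effect of condition on the mediator and the total effect of condition on symptoms. It does not protect the path from mediator slope to outcome slope, because youths are not randomised to improve in emotion regulation. Anything that makes a youth improve on both, or makes the same informant rate both as improved, creates an association between the two slopes that the model would read as a mediator effect. Putting the mediator first in time does not remove it.

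The stated covariate rule does not help. It tests association with condition, whereas a mediator-outcome confounder is defined by association with mediator and outcome. A baseline confounder is expected to be balanced between arms, so the rule will normally leave it out.

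At stake is the mechanism conclusion. It is one of the trial's three aims, has its own power statement in Sample Size and Power, and is presented in the Discussion as a main product of the trial.

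**Working it through.** The documents give no false-positive figure for Aim 2 to reproduce. The Aim 2 power statement (180 participants, a 0.36-SD indirect effect) gives no path sizes or variances, so it cannot be rebuilt. What follows is an illustration.

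**Inputs from the article.** N = 180 analysed; 1:1 allocation, so 90 per arm.

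**Assumed inputs.** The true mediator effect is zero. A shared cause correlates ρ with each slope within arm and is not adjusted for. FIRST shifts the mediator slope by *a* SD. Slopes have unit variance within arm. Mediation is declared when both paths are significant at two-sided 0.05. Slopes are treated as observed scores in single-level regressions, with no intercept term, so this is not the full latent growth model.

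**Step 1: how often the screen finds the confounder.** Under randomisation a baseline variable differs between arms at p<.05 in about 5% of trials, however strongly it predicts the two slopes. Simulation gave 4.7% to 5.2%.

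**Step 2: the spurious mediator path.** With condition in the model, the apparent effect of mediator on outcome is ρ × ρ = ρ²: 0.09, 0.16 and 0.25 for ρ = 0.3, 0.4 and 0.5. Its expected test statistic is ρ²√(N−3)/√(1−ρ⁴):

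- ρ = 0.3: 0.09 × 13.30/0.996 = 1.20, significant in 22.5% of trials
- ρ = 0.4: 0.16 × 13.30/0.987 = 2.16, significant in 57.8%
- ρ = 0.5: 0.25 × 13.30/0.968 = 3.44, significant in 93.0%

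**Step 3: the path from condition to mediator.** Its standard error is √(4/180) = 0.149.

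- *a* = 0.5: z = 3.35, significant in 91.8%
- *a* = 0.3: z = 2.01, significant in 52.1%
- *a* = 0: significant in 5%

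**Step 4: both paths significant (the product of steps 2 and 3, an approximation).**

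| FIRST effect on mediator | ρ = 0.3 | ρ = 0.4 | ρ = 0.5 |
|---|---|---|---|
| 0.5 SD | 21% | 53% | 85% |
| 0.3 SD | 12% | 30% | 48% |
| 0 | 1% | 3% | 5% |

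Simulation gave 21%, 53% and 84% for the first row and 12%, 29% and 47% for the second. At ρ = 0.2 and *a* = 0.5 it gave 7.5%, so a weak shared cause does little harm.

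**Step 5: what the remedies do (simulation, *a* = 0.5).** Adjusting only when the p<.05 screen flags the confounder gives 21% at ρ = 0.3 and 81% at ρ = 0.5, against 22% and 85% unadjusted in the same runs. Always adjusting for the confounder gives about 5% at both. Always adjusting for a baseline proxy that shares half its variance with the confounder gives 9% and 46%. Baseline covariates help but may not be enough, which is why a sensitivity analysis is needed.

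**Step 6: size of the spurious effect.** At *a* = 0.5 the indirect effect is 0.5 × ρ² = 0.045, 0.08 and 0.125 SD for ρ = 0.3, 0.4 and 0.5. Against the 0.36-SD planning value that is 13%, 22% and 35%.

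**The case against.** Several points on the other side stand.

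- **The screen is not the only covariate rule.** A reader might infer that it is. The article also allows medication use, gender and race/ethnicity in all outcome models, whatever their balance. That use is optional, framed as a check of robustness, and not aimed at mediator-outcome confounding.
- **Baseline severity is a weak example.** A reader might infer, from entry requiring "at least one scale on the Child Behavior Checklist (CBCL) [30] that is clinically elevated", that severe youths simply improve on everything and that the plan ignores this. The documents do not support that. Baseline levels are in the model as latent intercepts, and if slopes are regressed on them, confounding by those levels is largely handled. The criterion also selects on the CBCL, not on the affect or coping measures, so it does not show that severe youths fall further on both. Better candidates are comorbidity beyond the modelled scales, services outside the study, and shared-informant error: in Table 1 caregivers and youths rate both mediators and outcomes.
- **The percentages are not the trial's error rate.** They assume no baseline term, a chosen ρ and a real effect of FIRST on the mediator.
- **The article is cautious elsewhere.** Its Introduction calls this work an initial step, and the mediator is described as a candidate throughout. The disputed sentence could be read as naming a necessary condition only.
- **Some detail may sit in an analysis plan that is not shown.** A confounder list, a stated assumption and a sensitivity analysis commonly do, and their absence here is not held against the article.

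What remains is in the text itself: a conclusion that time order cannot carry, and a selection rule that works on the wrong association.

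**Conclusion.** The point holds in this limited form. As stated, Aim 2 claims more than a non-randomised mediator can support, and the main covariate rule leaves out a true mediator-outcome confounder about 95% of the time. If FIRST moves the mediator, a shared cause could be reported as mediation. Whether it would be depends on three things that the documents do not settle: how far FIRST moves the mediator, how strong the remaining shared causes are, and whether slopes are regressed on the intercepts. Across the assumed values the false-mediation rate runs from about 12% to 85% when FIRST moves the mediator by 0.3 to 0.5 SD, and stays at or below 5% when it does not. The primary comparison of FIRST with usual care in Aim 1 does not depend on this path.

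**What to change.** In the Aim 2 paragraph:

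1. Regress both the mediator slope and the outcome slope on condition, on both latent intercepts, and on a fixed set of pre-allocation variables whatever their balance between arms: for example age, gender, clinic, baseline medication and baseline number of diagnoses. Use this set for Aim 2 in place of the p<.05 screen.
2. Report the residual correlation between mediator slope and outcome slope at which the indirect effect falls to zero. Baseline covariates cannot remove every shared cause, shared-informant error in particular.
3. Replace the claim that a mechanism is established with wording such as: *results are consistent with mediation, assuming no unmeasured mediator-outcome confounding*. This agrees with the Introduction's description of the work as an initial step.

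The cost is a few more model parameters and a more modest conclusion. The covariates are already collected at baseline or known at allocation. The article plans no interim analyses and no analysis before data collection is complete, so the change can be fixed before results are seen.

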### Control Condition: Usual Care

UC is the treatment that is usually provided to youths at the partner clinic. This involves the standard training or on-boarding procedures provided to all partner clinic clinicians, and the routine supervision provided. Information on UC is collected via clinician surveys and via coding of a subset of session recordings. Clinicians in the UC condition are not provided access to the FIRST treatment manual, the FIRST training, consultation, online support, or the online performance feedback system.

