#### Therapy Integrity in Evidence-Based Interventions (TIEBI) [46].

The TIEBI is an observational coding system applied to recorded therapy sessions that assesses the presence/absence of the EST procedures of FIRST, and the competency with which these procedures are delivered (rated from 0 [not present] to 4 [expert]). Mean inter-coder agreement has been shown to be strong for both clinician adherence to FIRST (ICC [1, 1] = 0.87) and clinician competence in delivering FIRST procedures (ICC [1, 1] = 0.88) [28].

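### Aim 3 step 1, as written, pools both arms without a condition term and so loses precision for the clinician predictors

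*Protocol article*

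**What the plan says.** The Aim 3 paragraph under Planned Analyses in the protocol article fixes three things.

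- **Who is analysed:** "Data collected from clinicians at baseline in both conditions will be examined in multilevel regression models as level-2 (clinician-level) predictors". Both arms are in one model.
- **The outcome:** "we will use case-level mean TIEBI scores", averaged over the beginning, middle and end of each youth's treatment.
- **The sequence:** the four clinician measures are knowledge, attitudes, intentions and organizational climate. "In step 1, we will examine these four variables as predictors of implementation outcomes"; then "In step 2, we will test whether these four variables interact with treatment condition". No condition term is named for step 1.

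Three other places bear on the point. The TIEBI section says that the instrument "assesses the presence/absence of the EST procedures of FIRST, and the competency with which these procedures are delivered". The usual-care section says: "Clinicians in the UC condition are not provided access to the FIRST treatment manual, the FIRST training, consultation, online support", and it also withholds the feedback system. The Design section says that "clinicians are randomly allocated to 1 of 2 conditions", so condition does not vary within a clinician.

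**The concern.** Step 1 is the direct test of one of the stated research questions: whether clinician characteristics predict fidelity. Its outcome is the delivery of procedures that one arm is trained and supported to deliver and the other is not. If the arms differ on TIEBI and condition is not in the model, the difference goes into the variation between clinicians. That variation is the error term against which a clinician-level predictor is judged. The clinician random intercept does not help, because it carries this variance and does not remove it. A null step 1 result could then reflect unmodelled arm variance and not the absence of a relation between, say, EST knowledge and fidelity.

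**Working it through.** **The plan's own figure.** Sample Size and Power calls 180 youths adequate for a standardized coefficient of 0.25 in Aim 3, for predictors within the FIRST condition. It gives neither a power value nor an ICC for TIEBI, so the figure cannot be reproduced exactly. It also does not describe the pooled step 1 model.

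**Inputs from the protocol article.** 180 analysed youths and at least 24 clinicians, so 180/24 = 7.5 cases per clinician; 1:1 allocation of clinicians; four predictors.

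**Assumed inputs.** Clinician ICC for TIEBI 0.3; coefficient 0.4 per SD of the predictor; arm gap g of 0.5, 1 or 2 within-arm SDs; two-sided 5% test; predictors independent of each other and of condition.

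**Step 1: error variance of a clinician mean, condition in the model.** With within-arm variance set to 1: 0.30 + 0.70/7.5 = 0.393.

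**Step 2: what omission adds.** A 0/1 arm indicator split 1:1 has variance 1/4, so a gap g adds g²/4 to the between-clinician variance. This is 0.0625, 0.25 and 1.00 at gaps of 0.5, 1 and 2 SD.

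**Step 3: inflation of the standard error.** √[(0.393 + g²/4)/0.393]:
- g = 0.5: √(0.456/0.393) = 1.08
- g = 1: √(0.643/0.393) = 1.28
- g = 2: √(1.393/0.393) = 1.88

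**Step 4: simulation.** Regression of clinician means on four predictors, 24 clinicians, with and without condition:

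| Gap (SD) | Power with condition | Power without | SE increase from omission |
|---|---|---|---|
| 0 | 72% | 75% | none (the term itself costs 2 to 3 points) |
| 0.5 | 72% | 68% | 5% |
| 1 | 72% | 54% | 26% |
| 2 | 72% | 28% | 87% |

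The simulated increases are slightly below the formula because the model with condition spends one more degree of freedom. Type I error for a null predictor stays near 5% in both models at every gap.

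**Step 5: sensitivity.** The coefficient is now 0.25, as in the protocol's Aim 3 statement. The ICC is 0.02, which the protocol states for Aim 1 and not for TIEBI. With four predictors and 24 clinicians, power is about 76% with condition, against 63%, 39% and 15% without it at 0.5, 1 and 2 SD. At ICC 0.10 it is about 60%, against 50%, 32% and 15%. With 40 clinicians, ICC 0.02 and a 1 SD gap it is 84% against 56%. The direction is the same throughout; the size depends on the gap and the ICC.

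**The case against.** The strongest reply is that the article never says condition is excluded. Naming the four variables of interest need not be a full model statement, and an article may leave other terms to the full plan. That limits the point to the text as written. Still, the paragraph sets out a two-step sequence with named contents and introduces condition only in the second step, so an analyst following it would fit step 1 without condition. The covariate rule under Planned Analyses does not close the gap: it concerns baseline differences between the arms, not condition itself.

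Second, usual-care clinicians are denied the FIRST materials and support, not the procedures. Calming, reappraisal, problem solving and exposure may already be part of their practice, and Intervention Fidelity treats the amount of EST content in each arm as something to be determined. This stands: a gap is likely, but its size is unknown, and at 0.5 SD the loss is small under the ICC of 0.3.

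Third, a reader might infer that condition is the largest source of variance between clinicians. The documents do not support that. At a 1 SD gap the added variance is 0.25, below the assumed clinician variance of 0.30; only a larger gap exceeds it.

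Fourth, a reader might infer that step 1 is biased because better-informed clinicians may fall into one arm. With 24 clinicians the chance correlation between a predictor and condition does have an SD of about 1/√23 = 0.21. But clinicians are randomized and the predictors are measured at baseline, so no bias is expected. The chance correlation is the mechanism of the precision loss already counted, not a second harm.

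Finally, Aim 3 is exploratory and was not designed to be adequately powered. A step 2 model with the usual condition main effect would give estimates free of the arm gap. This stands and sets the weight of the point.

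**Conclusion.** The point holds as a minor improvement to the model. Followed as written, step 1 leaves any arm gap in TIEBI in the error term for the clinician predictors. Under the main assumptions (24 clinicians, 7.5 cases each, ICC 0.3, coefficient 0.4), power falls from about 72% to 68%, 54% or 28% as the gap goes from 0.5 to 1 to 2 SD. The gap, the ICC and the coefficient of 0.4 are assumptions, so the true loss could be a few points or more than forty. The harm is lost precision only, it is confined to step 1 of an exploratory aim, and no treatment-effect conclusion is touched.

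**What to change.** State that step 1 includes condition as a main effect alongside the four clinician variables, and that step 2 keeps it and adds the condition-by-predictor interactions. If condition was always meant to be in step 1, one clarifying phrase is enough. The change uses one clinician-level degree of freedom, which costs about 2 to 3 points of power if the arms turn out not to differ on TIEBI. It needs no new data and no change to the sample size.
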